**Table 2 T2:**
[figure not shown]
Data recording nodes from baseline to follow-up visits.

### Quality control and data management

2.11

Before the study, clinicians, statistical and methodological experts were invited to review and revise the study protocol many times. To ensure the accuracy and integrity of clinical data, the researchers should be trained on the consistency of scale evaluation to ensure that relevant personnel fully understand the research scheme and SOPs. The participants were selected in strict accordance with the plan, and the communication with the participants was strengthened to ensure the follow-up and medication compliance. All data is first recorded on paper CRF by researchers, and then double input electronic data acquisition system by electronic means. The whole process will be supervised by an independent quality inspector.

### Statistical analysis

2.12

Analysis data set including full analysis set (FAS), per-protocol set and safety analysis set.

(1)FAS refers to the case that has used the research drug at least once and has at least 1 main index measurement data after treatment. For the case data of failure to observe the whole treatment process, the last observation data is used to carry forward to the final result last observation carried forward (LOCF) of the study.(2)Per-protocol set: good compliance (treatment compliance ≥80%), no drug prohibition during the study, complete all follow-up, no serious violation of the study protocol.(3)Safety analysis set including all cases randomly enrolled and at least once used the study drug.

A detailed description of the cases of exfoliation and rejection, including the time and cause of exfoliation or rejection. Descriptive statistics indicate mean, standard deviation, maximum, minimum, median, confidence interval, frequency (constituent ratio), and so on. Per-Protocol (PP) analysis and FAS analysis were carried out for the main efficacy indexes at the same time; CMH method was used for the multicenter counting data, and *t* test and variance analysis were used for the measurement data; for the confounding factors that were difficult to control or not controlled before treatment, such as the imbalance between groups before treatment, least squares mean (LSMEAN) and 95% confidence limit or Logistic regression of analysis of covariance (ANCOVA) were used as covariates to determine the difference of curative effect among groups was eliminated. In addition to the main efficacy indicators, the superiority test was carried out with a statistical superiority test (Δ = 0). In the comprehensive analysis of TCM symptoms, the specific clinical manifestations (post-meal swelling, early satiety, epigastric pain, epigastric burning) and other symptoms were analyzed respectively. The statistical test was bilateral difference test, and those with *P* less than or equal to .05 were considered statistically significant. Statistical analysis will be performed by the SAS 9.2 software.

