#### Withdrawal of participants

2.4.1

Participants can voluntarily drop out at any time during the trial. All the participants who have filled in the informed consent form and screened for qualified entry into the trial, no matter when and why they quit, as long as they have not completed the prescribed observation period, are all cases of dropout. When participants drop out, the researcher should ask the reason, record the last time of taking medicine, complete the evaluation items that can be completed, and fill in the case report form (CRF) fall off reason table.

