#### The withdrawal decided by the investigator

2.4.2

(1)Participants with serious adverse events.(2)During the experiment, the participants had some complications or special physiological changes, so they were not suitable to continue the experiment.(3)In the trial, the participants used the banned drugs specified in the trial protocol due to poor compliance.(4)According to the judgment of the doctor, there might be dangerous events. To protect the participants, they should be removed from the clinical trial and receive other treatments, and the case will be treated as invalid.

All selected cases, no matter whether they fall off or not, should record and keep the research medical record and CRF. All the report forms of the lost cases are submitted to the clinical responsible unit for summary and statistical analysis.

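### LOCF is the only stated method for unfinished FAS cases, dosed participants with no post-treatment score are left out, and section 2.4.2 item (4) gives some of the same cases a conflicting status; the non-inferiority test can be biased in either direction

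*Protocol article*

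**What the plan says.** All references are to the protocol article.

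- **Section 2.12, analysis set:** "FAS refers to the case that has used the research drug at least once and has at least 1 main index measurement data after treatment".
- **Section 2.12, missing data:** for FAS cases not observed through the whole treatment, "the last observation data is used to carry forward to the final result last observation carried forward (LOCF) of the study". No other method is given.
- **Section 2.12, per-protocol (PP) set:** "good compliance (treatment compliance ≥80%), no drug prohibition during the study, complete all follow-up, no serious violation of the study protocol". The main efficacy measures are analysed in the PP set and the FAS together.
- **Section 2.4.1:** participants who leave for any reason, "as long as they have not completed the prescribed observation period, are all cases of dropout". When someone leaves, staff are to "record the last time of taking medicine, complete the evaluation items that can be completed".
- **Section 2.4.2, item (4):** of participants whom the doctor judges to be at risk, "they should be removed from the clinical trial and receive other treatments, and the case will be treated as invalid". The next paragraph adds: "All the report forms of the lost cases are submitted to the clinical responsible unit for summary and statistical analysis".
- **Section 2.5:** control effective rate about 60%, margin 13 points, one-sided alpha 0.025, a 20% allowance for missing data and loss, 192 recruited per group.
- **Section 2.10.3:** the main symptom score is taken at baseline and weeks 2, 4 and 6. Treatment lasts 4 weeks, so week 6 is off-treatment follow-up.

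**The concern.** There are two linked problems.

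First, LOCF treats a score taken before the end of treatment as if it were the end-of-treatment result, and counts that value as fully observed. The FAS definition also removes dosed participants who have no post-treatment score, and their reason for leaving may be related to outcome. In a non-inferiority trial, any handling that makes the arms look more alike than they are can produce a false positive conclusion. With 20% loss allowed for, the share of participants affected is not trivial. Running the PP analysis alongside does not settle the matter, because that set requires complete follow-up and so drops the same participants.

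Second, the text gives one kind of participant two statuses. A person removed under item (4) of section 2.4.2 who has had a dose and one post-treatment score belongs in the FAS with a carried-forward value under section 2.12, yet is invalid under section 2.4.2. Two analysts could follow the article faithfully and analyse different data.

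**Working it through.** **The conflict, read side by side.** Invalid is not defined.

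- If it means excluded, it contradicts the FAS rule, which keeps anyone who has "used the research drug at least once and has at least 1 main index measurement data after treatment".
- If it means failed, it contradicts LOCF, which keeps the last observed score whatever it is.
- The sentence sending the forms of all lost cases for statistical analysis fits the second meaning better but does not fix it.

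Neither meaning agrees with section 2.12.

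**Size of the possible bias.** The article gives no bias figure to reproduce. Taken from section 2.5 are the control rate of 60%, the margin of 0.13, one-sided alpha of 0.025 (z = 1.96) and n = 192 per arm. Assumed here are a true QZWTG rate of 47%, exactly at the margin, so that the test should succeed 2.5% of the time; the dropout shares; and the carried-forward rates. The end of treatment, week 4, is taken as the analysis point.

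D = pT − pC; SE = √[pT(1−pT)/nT + pC(1−pC)/nC]; P(false non-inferiority) = Φ((D + 0.13)/SE − 1.96), where T is QZWTG and C is Mosapride.

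*A. The 13-point deficit holds in everyone, and a share f has an earlier value carried forward.* Observed rate = (1−f) × week-4 rate + f × carried rate.

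Worked case, f = 20% in both arms, carried rate 35% in both:
- pT = 0.8×0.47 + 0.2×0.35 = 0.446
- pC = 0.8×0.60 + 0.2×0.35 = 0.550
- D = −0.104, SE = 0.0507
- P = Φ(0.026/0.0507 − 1.96) = 7.4%

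| f QZWTG / control | Carried rate QZWTG / control | D (points) | P |
|---|---|---|---|
| 0 / 0 | – | −13.0 | 2.5% |
| 10% / 10% | 35% / 35% | −11.7 | 4.4% |
| 20% / 20% | 35% / 35% | −10.4 | 7.4% |
| 10% / 10% | 37% / 45% | −12.5 | 3.1% |
| 20% / 20% | 37% / 45% | −12.0 | 3.9% |
| 20% / 10% | 35% / 35% | −12.9 | 2.6% |
| 15% / 5% | 35% / 35% | −13.6 | 1.9% |
| 20% / 5% | 35% / 35% | −14.2 | 1.4% |
| 10% / 20% | 35% / 35% | −9.2 | 11.3% |

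With equal dropout and equal carried rates, D does not depend on the carried rate. Rates of 20%, 30% and 40% give the same P to one decimal place.

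*B. Dropouts are true failures, but LOCF counts a share q of them as responders.* Observed rate = true rate + f×q, with q from 20% to 40%.
- 15% on QZWTG, 5% on control: D from −11.0 to −9.0, P from 5.9% to 12.2%.
- 10% in each arm: D = −13.0, P = 2.5%.
- 5% on QZWTG, 15% on control: D from −15.0 to −17.0, P from 0.9% to 0.3%.

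*C. Dosed participants with no score are true failures and drop out of the FAS.* Observed rate = true rate/(1−d), arm size = 192(1−d), where d is the share removed.
- d = 10% / 5% (QZWTG / control): 0.47/0.90 = 0.522 and 0.60/0.95 = 0.632, D = −10.9, P = 5.9%.
- d = 15% / 5%: D = −7.9, P = 16.2%.
- d = 5% in each arm: P = 1.8%. d = 10% in each arm: P = 1.3%.

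More loss on QZWTG lowers the error in A and raises it in B and C. The direction depends on which arm loses more and on why people leave.

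**The case against.** - **Exit scores.** A reader might infer that everyone who leaves before week 2 is excluded and that every later leaver carries a week-2 value. The article does not support this. Section 2.4.1 asks for completable evaluations at dropout, so an early leaver may have an exit score that admits them to the FAS, and that score may be the one carried. Someone leaving after week 4 already has a week-4 value. The exclusion applies only to those with no post-treatment score.
- **The 7.4%.** It needs the whole 20% to be LOCF cases with no difference between arms in the carried values. The allowance in section 2.5 also covers people with no score and losses after week 4, and nothing in the article shows that the arms would be alike at week 2. The figure illustrates what is possible and does not predict the trial's error rate.
- **Direction.** A reader might infer that these rules favour QZWTG. The scenarios above show that they can also make the test conservative.
- **The PP analysis.** It contains no LOCF values, so LOCF is not the only route to the result. But it removes the dropouts altogether, which is a selection problem of its own.
- **Scope of invalid.** The phrase belongs to item (4). The text does not clearly apply it to every investigator withdrawal.
- **Matters for an analysis plan.** The absence of sensitivity analyses from an article is no fault. LOCF, the FAS restriction and the invalid status are different, because the article states them. Leaving never-dosed participants out of the FAS is common practice and is not criticised here.

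**Conclusion.** The point holds in this form: single-value LOCF is the only stated method for unfinished FAS cases, dosed participants without a post-treatment score are left out, and item (4) of section 2.4.2 contradicts section 2.12 for some of the same people. The contradiction rests on the text alone. The bias is possible, and its direction is not established. Against a nominal 2.5%, the illustrations run from 1.4% to 11.3% in A, 0.3% to 12.2% in B and 1.3% to 16.2% in C. All rest on assumed true rates of 60% and 47%, assumed dropout and carried-forward rates, and 192 randomised per arm. With equal dropout and carried values, the figures are 4.4% and 7.4% at 10% and 20% LOCF cases. This should be changed, but it does not show that a positive result would be wrong.

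**What to change.** 1. Make the main week-4 analysis of the symptom score a repeated-measures model in every randomised and dosed participant. Handle baseline so that people with no later score still contribute, for instance as part of the response vector or through multiple imputation. If the off-treatment week-6 score enters the model, say in what role.
2. For the effective rate, multiply impute the score, then classify.
3. Keep LOCF as a sensitivity analysis, and add a tipping-point analysis that makes missing QZWTG outcomes progressively worse. Counting all dropouts as failures in both arms is not a substitute, since with equal dropout that too can shrink the difference.
4. Reconcile the invalid status in section 2.4.2 with the analysis-set rule in section 2.12, so that each withdrawn case has one stated handling. The rules for removing participants are not in question.
5. State how scores collected after a switch to other treatment are used. Used without comment, they could themselves pull the arms together.

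Cost: revised wording, modest programming, and more model assumptions to describe and defend.

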**Discussion::**

This trial will provide first-hand evidence on whether QZWTG is noninferior to Mosapride citrate tablet. There will be a new option for the treatment of FD if noninferiority is set up. In addition, the efficacy and safety of QZWTG in the treatment of FD will be evaluated, and the mechanism of QZWTG in the treatment of FD will be explored through the metabolomics of blood and urine. On the other hand, as far as we know, this study may be the largest trial of efficacy and safety of QZWTG in the treatment of FD, which has important application value.

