### Sample size calculation

2.5

According to previous study, the effective rate of Mosapride in the treatment of FD was around 60%.^[28–30]^ According to the ratio of test group: control group = 1:1, class I error *α* was 0.025 (1 side), class II error *β* was 0.2 (80%), and noninferior standard Δ was set as 13% to estimate the sample size, 160 participants are required for each group. Considering the possibility of missing data and loss of follow-up (20% in total), we will recruit a total of 384 participants for the 2 groups, with 192 participants in the experiment group and 192 participants in the control group.

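### Section 2.12 gives a two-sided test of no difference as its only test rule and never uses the 13% non-inferiority margin on which the trial was sized

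*Protocol article*

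**What the plan says.** The discussion part of the Abstract sets the aim: "This trial will provide first-hand evidence on whether QZWTG is noninferior to Mosapride citrate tablet". Section 2.5 (Sample size calculation) follows it. It takes as its starting point that "the effective rate of Mosapride in the treatment of FD was around 60" percent, uses an alpha that "was 0.025 (1 side"), and says that "noninferior standard Δ was set as 13% to estimate the sample size". The result is that "160 participants are required for each group", raised to 192 per group for losses.

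Section 2.12 (Statistical analysis) analyses the main efficacy indexes in both FAS and PP. For methods it says "CMH method was used for the multicenter counting data", and it gives t tests and analysis of variance for measurements, with covariate adjustment where groups are unbalanced. It mentions a superiority test with Δ = 0. Its closing rule is "The statistical test was bilateral difference test", with P of .05 or less counted as significant. The section contains no non-inferiority hypothesis, no 13%, and no comparison of a confidence limit with a margin. It mentions 95% limits only for descriptive statistics and adjusted estimates.

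Section 2.10.3 makes the primary outcome the change in main symptom score. It does not list an effective rate.

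**The concern.** Sections 2.5 and 2.12 test different null hypotheses. Section 2.5 sets out to reject that QZWTG is worse by 13 points or more. Section 2.12 sets out to reject that the two drugs are the same. Failing to reject sameness is not evidence that a 13-point deficit has been excluded, and it becomes more likely as the sample shrinks or the data get noisier.

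The headline conclusion is at stake. As written, the one result of the stated test that would support non-inferiority is a significant difference in favour of QZWTG, and the trial is not sized for that. A non-significant result leaves the main question unanswered and invites a conclusion that the data may not support.

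**Working it through.** **Inputs.** From section 2.5: control rate p = 0.60, margin Δ = 0.13, one-sided alpha 0.025 (z = 1.960), power 80% (z = 0.842), 1:1 allocation, 160 evaluable and 192 recruited per group. The test-arm rate is not stated. I assume 0.60 (equal efficacy), and 0.47 for a drug exactly at the margin.

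**The plan's own figure.** n = (1.960 + 0.842)² × 2p(1−p) / Δ² = 7.849 × 0.48 / 0.0169 = 222.9, so 223 per group. The stated 160 is not reproduced with equal rates. A test-arm rate of 62% gives 166 and 62.5% gives 155. That is a separate matter. I use 160 and 192 below because they are the plan's numbers.

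**1. Alpha.** Two-sided 0.05 has 0.025 in each tail, equal to one-sided 0.025. A two-sided 95% interval would serve the sizing test if its lower limit were set against −13 points.

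**2. Where the two rules part.** With 60% in both arms, SE = √(0.48/n) and half-width = 1.96 × SE.

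| n per group | SE | Half-width | P>.05 needs d above | Margin met needs d above |
|---|---|---|---|---|
| 160 | 0.0548 | 10.7 points | −10.7 | −13 + 10.7 = −2.3 |
| 192 | 0.0500 | 9.8 points | −9.8 | −13 + 9.8 = −3.2 |

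Here d is the observed rate on QZWTG minus that on mosapride. Between −10.7 and −2.3 points at 160 (−9.8 and −3.2 at 192), the difference test is non-significant and non-inferiority is not shown.

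**3. A drug truly 13 points worse (47% v 60%).** Pooled SE under no difference = √(2 × 0.535 × 0.465 / n), which is 0.0558 at 160. True SE = √((0.24 + 0.2491)/n), which is 0.0553 at 160. The chance of P>.05 is about Φ((−0.13 + 1.96 × 0.0558)/0.0553) = Φ(−0.37) = 0.354. The same formula gives 0.275 at 192. Exact binomial enumeration gives 0.354 at 160 and 0.284 at 192. The margin rule (lower 95% limit above −13 points) passes in 0.026 and 0.023.

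**4. A drug truly equal (60% v 60%).** Exact enumeration:

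| n per group | P>.05 | Margin met | P>.05 but margin not met |
|---|---|---|---|
| 160 | 0.952 | 0.658 | 0.318 |
| 192 | 0.948 | 0.745 | 0.229 |

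So about 32% of trials at 160, and 23% at 192, would be non-significant without showing non-inferiority.

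**The case against.** **The sentence on Δ = 0.** It opens with an expression that can mean either besides or except for the main efficacy indicators. Read as except for, it sets the main outcome apart from the superiority test, which fits section 2.5. That reading is fair, but it lifts only the Δ = 0 test. The later bilateral-test sentence has no such exception, and no margin test is put in its place.

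**A condensed article.** The SAP may hold the proper test. The point does not rest on silence, however: the article states a test rule that conflicts with its own design.

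Four stronger readings are tempting and are not supported:

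- **That the plan declares P>.05 to be non-inferior.** It says only what counts as significant. The 35% and 28% hold only if someone draws that inference.
- **That the alpha levels contradict each other.** They do not (step 1).
- **That a significant but trivial deficit would be counted as failure.** At 192 per group a significant deficit is at least about 9.8 points, so the lower limit is near −9.8 − 9.8 = −19.6 and the margin is missed anyway. Enumeration gives essentially zero probability of a significantly worse result that meets the margin.
- **That success in either FAS or PP would do.** The article says both are analysed and gives no success rule. That detail may properly sit in the SAP.

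**Conclusion.** The point holds, as a conflict in the null hypothesis and an unused margin. The only test rule stated in section 2.12 cannot answer the question posed in the Abstract and sized in section 2.5.

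The sizes in steps 3 and 4 are on the effective-rate scale. They assume 60% on mosapride, 47% or 60% on QZWTG, an unstratified comparison, and 160 or 192 analysed per group. They do not carry over to a symptom-score change, for which the protocol gives no margin. That mismatch makes the gap wider: a t test on a score has no way to use a 13-point margin on a rate.

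This should be settled before the analysis, because it decides whether the main conclusion can be drawn at all.

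**What to change.** In section 2.12 and in the SAP:

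1. Name the endpoint to which the 13% margin applies. Section 2.5 uses an effective rate and section 2.10.3 a symptom-score change, so the two must be reconciled first. If the rate is kept, it needs a definition. If the score change is kept, it needs a margin on its own scale.
2. If the rate carries the margin, conclude non-inferiority only if the lower limit of the two-sided 95% confidence interval for the stratified difference (QZWTG minus mosapride) is above −13 points, in both FAS and PP. A Mantel-Haenszel or Miettinen-Nurminen interval would serve.
3. Test Δ = 0 on that endpoint only after step 2 is met.
4. Limit the bilateral difference tests to the other outcomes.

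Steps 2 to 4 cost a few sentences and need no new data. Step 1 is a real decision about the primary endpoint and must be made without sight of unblinded results. The change leaves the sample size as it is. With 60% in both arms, the margin test has about 66% power at 160 per group and about 74% at 192, below the intended 80%.

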**Methods::**

This study is a multicenter, randomized, double-blinded, double-placebo, positive drug parallel controlled clinical study. The experiment will be carried out in 8 hospitals at the same time, and a total of 384 cases of participants will be randomly assigned to the experimental group and the control group (n = 192). The experimental group will be given QZWTG and Mosapride citrate tablet placebo, and the control group will be given QZWTG placebo and Mosapride citrate tablet. After 4 weeks of intervention and 2 weeks of follow-up, the efficacy and safety of QZWTG in patients with FD will be observed. The primary outcomes are the change in the main symptom score. The secondary outcomes include TCM syndrome evaluation, the change of the Hamilton anxiety scale and the Hamilton depression scale, and advanced events. This study will explore the biological mechanism of QZWTG in the treatment of FD through the results of blood and urine metabolomics.

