#### Primary and secondary outcomes

2.10.3

The primary outcomes are the change of the main symptom score contains an evaluation of postprandial fullness discomfort, early satiety, epigastric pain, epigastric burning sensation and so on. The main symptom score mainly utilized to assess the severity of symptoms and distinguish between EPS and PDS. The score will be assessed at baseline and week 2, week 4, week 6.

Owing to psychosocial factors likely play a role in FD,^[31–33]^ with greater FD symptom severity correlated with depression and somatization, this trial also includes the anxiety and depression assessment form in the assessment of secondary outcomes. The secondary outcomes mainly include TCM syndrome evaluation, the change of the Hamilton anxiety scale and the Hamilton depression scale, which will be measured at baseline and every 2 weeks during the treatment period to evaluate the changes of patients’ mental and psychological status, biochemical indicators, and changes of blood metabonomics and urine metabonomics (Table 2).

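### The only significance rule in section 2.12, an unadjusted two-sided P≤.05 with no exception, should not govern individual metabolites, which section 2.10.3 places among the secondary outcomes

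*Protocol article*

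**What the plan says.** **Status of metabolomics.** Section 2.10.3 (Primary and secondary outcomes) ends its sentence on secondary outcomes with "biochemical indicators, and changes of blood metabonomics and urine metabonomics". The abstract differs. Its Methods paragraph lists the secondary outcomes without metabolomics and then adds, as a separate sentence, "This study will explore the biological mechanism of QZWTG in the treatment of FD through the results of blood and urine metabolomics". The abstract's Discussion paragraph repeats that the mechanism "will be explored through the metabolomics of blood and urine".

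**Testing rule.** Section 2.12 (Statistical analysis) assigns the t test and analysis of variance to measurement data. It then says "In addition to the main efficacy indicators, the superiority test was carried out with a statistical superiority test", with a difference of zero as the reference. It closes with a general rule: "The statistical test was bilateral difference test", and P values "less than or equal to .05 were considered statistically significant". No outcome is exempted from this rule, and section 2.12 does not mention metabolomics.

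**The concern.** A threshold of .05 per test suits a handful of clinical secondary outcomes. It does not suit a set of outcomes that may contain many variables, each tested in two matrices. Metabolite levels are measurement data and are not the main efficacy indicator. A reader who follows section 2.12 to the letter would therefore run a t test on each metabolite and call it significant at P≤.05. The list obtained would contain chance findings in proportion to the number of metabolites tested, even if the two drugs had the same metabolic effects.

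Exploring the mechanism is a stated aim of the trial, and that list would be the evidence for it. An analysis plan that followed this section faithfully would inherit the rule, and one that controlled false discoveries would depart from it. The article's two accounts of metabolomics, secondary outcome in one place and exploration in the other, leave open which standard applies.

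**Working it through.** The document gives no number of metabolites and no expected number of false positives, so there is no figure of its own to reproduce on this point.

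**Inputs**
- Threshold: two-sided 0.05 per test (section 2.12).
- M, the number of metabolite tests over blood and urine together: not given, so assumed from 20 to 1,000.
- Share of metabolites that truly differ, π: not given, so assumed from 1% to 20%.
- Power per metabolite: not given, so assumed to be 80%. The 80% in section 2.5 belongs to the primary comparison and says nothing about metabolites.

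**Step 1: chance findings if nothing differs.** The expected number is 0.05 × M. This holds whether or not the metabolites are correlated. For independent tests, the probability of at least one is 1 − 0.95^M.

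| M | Expected chance findings | Probability of at least one |
|---|---|---|
| 20 | 1 | 64% |
| 50 | 2.5 | 92% |
| 100 | 5 | 99.4% |
| 200 | 10 | about 100% |
| 500 | 25 | about 100% |
| 1,000 | 50 | about 100% |

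For two dozen expected chance findings, M must be 24/0.05 = 480.

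**Step 2: false share of the declared metabolites.** Taken as a ratio of expected counts, this is 0.05(1 − π) / [0.05(1 − π) + 0.80π]. It does not depend on M.

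| π | Calculation | False share |
|---|---|---|
| 1% | 0.0495 / (0.0495 + 0.0080) | 86% |
| 5% | 0.0475 / (0.0475 + 0.0400) | 54% |
| 10% | 0.0450 / (0.0450 + 0.0800) | 36% |
| 20% | 0.0400 / (0.0400 + 0.1600) | 20% |

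A small panel therefore produces few chance findings in number, but the share of its declared list that is false can still be large.

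**The case against.** The strongest reply is that section 2.12 never mentions metabolites. Its methods read as a clinical efficacy analysis, and the P≤.05 sentence comes directly after the analysis of symptoms. The platform, the choice between a targeted and an untargeted approach, and false discovery control are details that a condensed article commonly leaves to the full protocol or the SAP, neither of which is at hand. The abstract already uses exploratory wording.

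Much of this stands. That no false discovery method is named would be no finding by itself. The rule reaches individual metabolites only because it is general, not because the text applies it to them. The abstract's wording already supplies part of the remedy.

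Three stronger readings are tempting, and the document supports none of them:
- **That dozens of metabolites will be falsely declared.** This needs about 480 tests or more, and the document states no count. For 20 to 100 tests the expected number is 1 to 5.
- **That the chance findings recur at each post-baseline visit.** The metabolomics sampling times cannot be seen, because Table 2 is not shown. The two-weekly schedule in section 2.10.3 most naturally belongs to the Hamilton scales.
- **That the list will be presented as the established mechanism.** The abstract says only that the mechanism will be explored.

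The reply does not remove what is written: a rule without exceptions, and an outcome in the secondary list for which that rule is unsuitable.

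**Conclusion.** The point holds as a minor one. Followed literally, section 2.12 would declare about 5% of truly unchanged metabolites significant. The count is 0.05 × M with M unknown: 1 to 5 for 20 to 100 tests, and 25 to 50 for 500 to 1,000. The false share of the declared list runs from about 20% to 86% over the assumed range of true effects, and it also rests on the assumed 80% power. These ranges show how the rule behaves and do not forecast this trial's results. The primary non-inferiority conclusion is unaffected. What is exposed is the exploratory aim concerning mechanism.

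**What to change.** 1. In section 2.12, state that the P≤.05 rule does not govern individual metabolites.
2. In the same place, state that change from baseline will be compared between arms for each metabolite, with Benjamini-Hochberg false discovery rate control within each matrix (blood and urine separately), at a level named in advance, for example 0.05.
3. Label metabolomics exploratory in both section 2.10.3 and the abstract, so that its status is the same throughout.

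This costs a sentence or two of text and trivial programming. It needs no new data and leaves the primary analysis unchanged. The downside is a shorter list of significant metabolites.
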